### Sampling

The study will employ a **convenience sampling method**, recruiting all consecutive eligible individuals with diabetes mellitus (DM) visiting physician clinics and eye care settings who meet the standard inclusion and exclusion criteria and provide informed consent. While convenience sampling is utilized, potential sources of bias include **selection bias, site-specific variation, differential access to care and Observer Bias**. To mitigate these, systematic recruitment will be ensured by enrolling all eligible patients consecutively at each site, reducing the likelihood of preferential selection. Recruitment will take place across multiple physician clinics and eye care settings to improve representativeness and minimize site-specific variation. Differential access to care will be monitored by assessing demographic and clinical characteristics of enrolled participants, allowing adjustments to recruitment strategies if needed. To prevent observer bias, standardized screening protocols and training for healthcare personnel will be implemented, ensuring consistency in recruitment and data collection. These measures aim to enhance the validity and generalizability of the findings while acknowledging the inherent limitations of convenience sampling.

### Sample size

We calculate the sample size to detect meaningful differences in the disease staging of patients between two arms at their first eye consultation. Based on the historic data from LVPEI, we assume a 50% prevalence of STDR among DR patients in the SOC arm. Also, we assume that the prevalence of STDR in the intervention arm at the time of screening in the diabetes clinic would be much lower (approximately 10%). However, patients in early stages of DR may not comply with the referral and hence the prevalence of STDR among patients who complete their first ophthalmology visit may be higher (approximately 25%). Based on these estimates, to achieve a power of 80% with a Type-I error rate of 5%, we estimate a sample size of 60 patients in each arm. Since the additional intervention required for the study is minimal (a short check-up using a camera), we expect that about 80% of the eligible patients will consent to participate. Thus, we will need 75 patients with DR to be identified in the intervention arm. Further, based on the historic data at the IDEA clinics, we estimate that 20% of all new registering diabetic patients will have DR. Thus, we will plan to register and screen 375 new diabetic patients each at IDEA clinics (intervention) and LVPEI clinics (SOC arm).

To evaluate the AI tool’s diagnostic accuracy with sensitivity and specificity set at 80%, a sample size of 246 DR-positive cases is required for sensitivity analysis, and 246 DR-negative cases for specificity analysis, assuming a 95% confidence level and a margin of error of ±5%.Given the estimated 20% prevalence of diabetic retinopathy (DR) in the screened population, a total of 1230 patients will be screened to ensure adequate representation of both DR-positive and DR-negative cases.

To assess patient satisfaction, a sample size of **316 patients** will be selected from both the AI-enabled and routine eye care pathways, calculated to detect a difference in satisfaction rates (80% vs. 65%) with a **95% confidence level** and a **margin of error of ±5%**. Random sampling will be employed to ensure unbiased selection of participants from each pathway. This method will involve assigning unique identifiers to eligible patients and using a randomization tool to select participants, ensuring the sample is representative of the study population.

Patient satisfaction will be assessed using a structured survey that includes validated tools like the **Patient Satisfaction Questionnaire (PSQ-18)** and custom questions specific to the AI-enabled DR screening program. The survey will use a **Likert scale** (e.g., 1 = very dissatisfied to 5 = very satisfied) to evaluate domains such as accessibility, process experience, and outcome satisfaction. Surveys will be administered after screening and follow-up visits, either digitally or on paper, to capture immediate and longitudinal feedback. Responses will be anonymized and analyzed to assess overall satisfaction and identify areas for improvement.

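### The intervention arm's chain from 60 to 375 patients has no term for referral attendance, so if the primary comparison rests on 375 screened, its power at the stated rates is about 56-66%, not 80%

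*Protocol article*

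**What the plan says.** All the figures are in the Sample size section of the protocol article.

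- **Comparison.** The aim is to "detect meaningful differences in the disease staging of patients between two arms at their first eye consultation".
- **SOC rate.** "we assume a 50% prevalence of STDR among DR patients in the SOC arm".
- **Intervention rate at screening.** "the prevalence of STDR in the intervention arm at the time of screening in the diabetes clinic would be much lower (approximately 10" per cent).
- **Intervention rate at the eye clinic.** "the prevalence of STDR among patients who complete their first ophthalmology visit may be higher (approximately 25" per cent). The reason given is that "patients in early stages of DR may not comply with the referral".
- **Size.** With 80% power and 5% type I error, the section arrives at 60 patients per arm.
- **Recruitment chain.** It allows for 80% consent, justified by how little the camera check asks of patients: "Thus, we will need 75 patients with DR to be identified in the intervention arm". It then applies a 20% DR prevalence: "we will plan to register and screen 375 new diabetic patients each at IDEA clinics (intervention) and LVPEI clinics (SOC arm").
- **AI accuracy objective.** This is sized separately, again at 20% prevalence: "a total of 1230 patients will be screened".

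**The concern.** The 60 intervention patients must be DR patients who reach the eye clinic, because the endpoint is staging there and the 25% is defined among those who complete that visit. The only losses in the chain are refusal of consent and absence of DR. Non-attendance after referral is used to raise the intervention rate from 10% to 25%, which shrinks the effect. It is never used to reduce the number of patients who contribute to that rate.

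At stake is the stated 80% power of the primary comparison. If 375 screened at the diabetes clinics is treated as enough, the intervention arm would have about half the patients that the calculation calls for, or fewer.

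**Working it through.** **1. The plan's own figures.** Inputs: 50% and 25%, two-sided 5% (sidedness is not stated and is assumed), 80% power. The mean proportion is 0.375.

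n = [1.96 × √(2 × 0.375 × 0.625) + 0.842 × √(0.25 + 0.1875)]² / 0.25² = 57.7, so 58 per arm. The unpooled formula gives 55. The stated 60 is reproduced within rounding. The chain 60/0.80 = 75 and 75/0.20 = 375 is exact.

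**2. Attendance implied by the stated rates.** Let a be the attendance of STDR patients and b that of the other DR patients. With 10% STDR at screening and 25% among attenders:

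0.10a / (0.10a + 0.90b) = 0.25, so overall attendance is 0.10a + 0.90b = 0.40a.

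Since a cannot exceed 1, attendance is at most 40%. Per 100 DR patients, that is all 10 with STDR and 30 of the other 90.

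The 10% must be read as a share of DR patients. If it were a share of everyone screened, with 20% DR, STDR would be 10/20 = 50% of DR patients, and losing early-stage patients could not bring that down to 25%.

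**3. Evaluable intervention patients from 375.**

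- If the 375 have already consented: 375 × 0.20 × 0.40 = 30.
- If consent is still to be applied: 375 × 0.80 × 0.20 × 0.40 = 24.

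**4. Power for 50% against 25%.** Power = Φ[(0.25 − 1.96 × s₀)/s₁], where s₀ is the pooled and s₁ the unpooled standard error of the difference. Example with 60 SOC and 24 intervention patients: s₀ = 0.1195, s₁ = 0.1094, so Φ(0.144) = 55.7%. The SOC arm is shown at 60 (the target) and at 75 (375 × 0.20 with no consent loss).

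| Intervention n | 60 SOC | 75 SOC |
|---|---|---|
| 60 (as planned) | 81.6% | – |
| 24 | 55.7% | 58.2% |
| 30 | 63.0% | 66.0% |

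Exact power of the uncorrected chi-square test with 60 SOC patients is 55.8% (24) and 64.1% (30).

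**5. Sensitivity to the two approximate rates.** The attendance cap is the screening rate divided by the visit rate. The power ranges below recompute both the cap and the effect, and span both consent readings and 60 to 75 SOC patients.

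| At screening | At visit | Cap | Intervention n | Power |
|---|---|---|---|---|
| 10% | 25% | 40% | 24-30 | 56-66% |
| 12% | 25% | 48% | 29-36 | 62-72% |
| 10% | 22% | 45% | 27-34 | 71-81% |
| 12% | 22% | 55% | 33-41 | 77-86% |
| 10% | 30% | 33% | 20-25 | 34-41% |

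**6. Screening needed for 60 attenders.** 60/0.40 = 150 consenting DR patients. 150/0.20 = 750 consented and screened. 750/0.80 = 937.5, so about 938 approached.

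**7. If the 1230 were used.** 1230 × 0.20 × 0.40 = 98 attenders, or 98.4 × 0.80 = 79 if consent is still to be applied. Power is 86.5% (79) or 89.4% (98) with 60 SOC patients, and 90.1% or 92.8% with 75.

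**The case against.** The strongest reply is that the study will screen 1230 patients anyway. The Sample size section sizes several objectives separately, and the largest requirement would normally govern. The Sampling section recruits all consecutive eligible patients, and nothing says that recruitment stops at 375. The AI cameras are spread over four facilities, which matches the four diabetes clinics. On that reading the primary comparison would have ample power. This largely stands as a point about practical harm. A reader might infer that 375 and 1230 are incompatible targets, but the documents do not support that: they serve different objectives, and one can contain the other. What remains is that the protocol article never links them and gives 375 as the number for this comparison.

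A second reply is that both rates are approximate. This also stands. At 12% and 22% power could reach 77-86%, so 56-66% is the result at the stated values and not a forecast. The rates can err the other way too (34-41% at 10% and 30%), and any STDR patient who fails to attend lowers the numbers further.

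Third, the 24 and the 938 hold only if consent is applied after the count of 375. The Selection of participants section seeks consent before study procedures, which favours 30 and 750. Both readings are therefore shown.

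Finally, better attendance would bring the visit rate towards 10%, and 10% against 50% needs only 20 per arm. That is correct, but it abandons the 25% scenario on which the 60 and the 80% power rest.

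**Conclusion.** The point holds in a conditional form. On the plan's own rates, 375 screened at the diabetes clinics yield at most 24-30 evaluable intervention patients instead of 60. Power is then about 56-63% with 60 SOC patients, or 58-66% with 75, instead of 80%. The missing attendance term is certain. The size of the loss depends on four things: the primary comparison resting on the 375; STDR rates close to 10% and 25%; full attendance by STDR patients, which is the best case; and a two-sided 5% test.

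A reader might go further and conclude that the study as a whole is underpowered. The documents do not support that, because the 1230 could supply enough attenders if they are screened at the diabetes clinics and counted in this comparison. As written, though, the stated sample size does not deliver the stated power, and the section should be corrected.

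**What to change.** 1. Add the attendance term for the intervention arm: 60/0.40 = 150 consenting DR patients, which means about 750 consented and screened or about 938 approached. Say which of these counts the target refers to, and note that 40% is an upper bound.
2. State whether the 1230 planned for the AI objective are screened at the diabetes clinics and also serve the primary comparison. If so, give the expected attenders (about 79-98) and the power (about 86-93% with 60 to 75 SOC patients).
3. If the primary comparison is instead limited to 375, restate its power as about 56-66% and show how it varies with the assumed rates.

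The cost is a rewording of the Sample size section, with no patients beyond the 1230 already planned. The Study timeline section says that recruitment is under way, so this should be settled before 375 is taken as sufficient. Observed referral attendance can then be checked against the 40%.

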### Program outcomes

The program’s outcomes will be evaluated through metrics such as screening uptake rate, sensitivity, and specificity of AI versus manual system, ROC Curve for AI Diagnostic Accuracy for diagnosis of DR, referral rate, cost-effectiveness, patient and provider satisfaction, follow-up rates, and long-term outcomes. These outcomes will help determine the program’s impact on patient health and healthcare costs. Due to the formatting constraints of the CTRI registry, certain fields were filled in a specific way, which might lead to minor discrepancies between the reported outcomes in the manuscript and the CTRI registry. (Table 1 shows the outcome measurement indicators for the project.).

**Table 1 pone.0324382.t001:** Outcome measurement indicators: SMART DROP project.

Outcome	Definition	Numerator	Denominator
Screening uptake rate	Proportion of eligible patients who underwent DR screening out of the total eligible population.	Number of eligible patients who underwent DR screening	Total number of eligible patients in the population
Sensitivity of AI system	Proportion of true positive DR cases correctly identified by the AI system.	Number of true positive DR cases identified by the AI system	Total number of true DR cases confirmed by manual grading
Specificity of AI system	Proportion of true negative cases correctly identified by the AI system.	Number of true negative DR cases identified by the AI system	Total number of non-DR cases confirmed by manual grading
ROC curve for AI diagnostic accuracy	A graphical plot showing the diagnostic ability of the AI system by plotting true positive rate (sensitivity) against false positive rate (1-specificity).	True positive rate (sensitivity)	False positive rate (1-specificity)
Referral rate	Proportion of screened patients referred for further examination or treatment.	Number of patients referred for further examination or treatment	Total number of patients referred
Cost effectiveness	Ratio of the total costs associated with the screening program to the health outcomes achieved, typically measured as cost per quality-adjusted life year (QALY).	Total costs of the screening program	Total health outcomes achieved (e.g., QALYs gained, cases of blindness prevented)
Patient satisfaction	Proportion of patients reporting satisfaction with the DR screening process and outcomes.	Number of patients reporting satisfaction	Total number of patients who completed the satisfaction survey

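### The ±5% margin stated for the satisfaction sample of 316 does not hold for the 80% vs 65% difference, nor for both pathway rates, though the size is adequate to detect that difference

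*Protocol article*

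**What the plan says.** The third paragraph of Sample size in the protocol article sets the number for the satisfaction survey: "a sample size of 316 patients will be selected from both the AI-enabled and routine eye care pathways". It gives the basis as "calculated to detect a difference in satisfaction rates (80% vs. 65"%), "with a 95% confidence level and a margin of error of ±5"%. It adds that "Random sampling will be employed to ensure unbiased selection of participants from each pathway".

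The paragraph gives no power for this comparison. The only power in the section belongs to the disease-staging comparison: "to achieve a power of 80% with a Type-I error rate of 5%, we estimate a sample size of 60 patients in each arm". The text does not say whether 316 is the total or the number per pathway, or whether the ±5% refers to the difference, to each pathway's rate or to an overall rate.

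Under Objectives, the second secondary objective is to evaluate satisfaction in the AI-enabled program against the routine pathway. The Statistical analysis section plans chi-square tests for categorical outcomes. In the outcome table under Program outcomes, the denominator for satisfaction is "Total number of patients who completed the satisfaction survey".

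**The concern.** The sentence joins two different kinds of sample size justification. Detecting 80% against 65% is a hypothesis test, which needs a significance level and a power. A confidence level with a margin of error is a precision target, which needs a named quantity to be estimated. One number can serve both aims only if it is checked against both, and the quantity named here is a difference between two groups, whose interval is wider than that of either rate alone.

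A reader of the results would expect the satisfaction difference to be known to within 5 points. If the true half-width is nearly twice that, the precision claimed in the plan will not appear in the report. A secondary objective is affected; the primary staging comparison is not.

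**Working it through.** **Inputs from the Sample size section:** rates p1 = 0.80 and p2 = 0.65, so the difference is 0.15 and the mean rate 0.725; 95% confidence, read as two-sided 5% (z = 1.96); stated size 316; stated margin 0.05.

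**Assumptions, because the text is silent:** equal numbers in the two pathways, and every selected patient completes the survey. Non-response would widen every interval below.

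**1. Can 316 be reproduced?**

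Pooled two-proportion formula, per pathway:

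n = [1.96·√(2·0.725·0.275) + z_power·√(0.80·0.20 + 0.65·0.35)]² / 0.15²

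The two square roots are √0.39875 = 0.6315 and √0.3875 = 0.6225.

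- 80% power (z = 0.842): 138 per pathway, 276 in total.
- 85% power (z = 1.036): (1.2377 + 0.6452)² / 0.0225 = 157.6, so 158 per pathway and 316 in total. This is an exact match.
- 90% power (z = 1.282): 185 per pathway, 370 in total.

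Precision formula for one proportion, n = 1.96²·p(1−p)/0.05²:

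- p = 0.80: 246
- p = 0.725: 307
- p = 0.65: 350
- p = 0.50: 385

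None of these equals 316; the mean-rate version (307) is within 3% of it.

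**2. What margin does 316 give?**

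Difference: half-width = 1.96·√[(0.16 + 0.2275)/n], with n per pathway. Single rate: half-width = 1.96·√[p(1−p)/n].

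| Quantity | 158 per pathway (316 total) | 316 per pathway |
|---|---|---|
| Difference, 80% vs 65% | ±9.7 points | ±6.9 points |
| Rate of 80% | ±6.2 | ±4.4 |
| Rate of 65% | ±7.4 | ±5.3 |

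One rate of 72.5% pooled over 316 patients: 1.96·√(0.725·0.275/316) = ±4.9 points.

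**3. What would ±5 points on the difference need?**

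n = 1.96²·0.3875/0.05² = 595.4, so 596 per pathway, or 1192 in total.

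**4. What power does 316 give for 15 points?**

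z_power = (0.15·√n − 1.2377)/0.6225.

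- n = 158 per pathway: (1.8855 − 1.2377)/0.6225 = 1.04, power 85.1%.
- n = 316 per pathway: (2.6665 − 1.2377)/0.6225 = 2.30, power 98.9%.

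**The case against.** The strongest defence is that the protocol never says what the ±5% applies to. The preceding paragraph of the same section uses the same confidence level and margin for single proportions, and its 246 is exactly the one-proportion result at 80%. Read that way for satisfaction, 316 patients give ±4.9 points for an overall rate of 72.5%, and 316 per pathway gives ±4.4 for the 80% pathway. This stands as far as it goes: a reader might infer that ±5% fails under every reading, and that is not so. But the overall rate averages the two pathways, while the objective and the sizing sentence both compare them; and 316 per pathway still misses ±5 in the 65% pathway (±5.3).

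A second defence is that nothing is underpowered. That is correct. Power is at least 85% for 15 points whether 316 is the total or the number per pathway, the planned test is a comparison of proportions, and no decision rule uses the ±5%. A condensed article may also leave the power for a secondary survey to a fuller document. The silence on power is therefore a weak point by itself; it matters here because the basis that is given does not fit.

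A third defence concerns the total-or-per-pathway question. Elsewhere the section says explicitly when a number is per arm, whereas here the patients "will be selected from both the AI-enabled and routine eye care pathways", which reads more naturally as a total. This also stands, and little weight should rest on a possible doubling of the survey.

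**Conclusion.** The stated "margin of error of ±5"% is wrong for the comparison it accompanies. On the difference, the half-width is ±9.7 points if 316 is the total and ±6.9 if it is per pathway. Under neither reading do both pathway rates reach ±5. Only a rate pooled over both pathways does so on the more natural reading of 316 as a total. These figures assume equal split, full response and the protocol's own rates.

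Three stronger conclusions might be inferred, and the documents do not support them:

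- That 316 was derived as an 85%-power design with 158 per pathway. The match is exact, but neither 85% nor 158 appears in the protocol, and other calculations come close (307 from the mean-rate precision formula; 310 and 314 from unpooled and arcsine versions at 85% power). It is the most plausible origin, not an established one.
- That the survey is too small. It is adequate to detect 15 points.
- That the plan is infeasible because 596 exceeds the 375 patients per arm planned for the staging comparison. Nobody plans 596; the figure only shows how far ±5 lies from what 316 delivers.

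What remains is an incorrect precision claim on a secondary objective, worth correcting because the correction is cheap.

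**What to change.** Delete the ±5% margin from the satisfaction paragraph and justify 316 as a comparison of two proportions. The sponsor should confirm from its own records whether 316 is the total or the number per pathway, and what power was used; these should not be filled in from the numerical match alone.

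If 316 is confirmed as the total, the sentence can state: 158 patients per pathway, two-sided alpha 5%, about 85% power for 80% against 65%, and an expected 95% confidence interval half-width of about ±10 points on the difference. If it is confirmed as the number per pathway, the corresponding figures are about 99% power and ±6.9 points.

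The cost is one sentence and a less favourable stated precision. The correction does not itself require a change to the sample size, the survey or the planned test.

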### Cost-effectiveness analysis

The evidence on cost-effectiveness of screening for DR using digital technologies is mixed. For instance Avidor et al. found that the results varied from not being cost-effective to being cost-effective to being cost-saving based on the context and the frequency and modality of the screening and the use of telemedicine [35]. Given the resource constraints in an LMIC like India, it is imperative that the AI solutions proposed are cost-effective (preferably cost-saving) if they are to be adopted at scale.

We will calculate the incremental costs incurred at the diabetes clinic to set up the systematic screening program and an integrated referral pathway. This comprises the cost of additional personnel, if any, and amortisation of the equipment and the cost of personnel involved in grading of the images. Additional cost components will include personnel training and capacity building at the clinic level, costs of AI model integration and periodic validation, maintenance and software updates for AI and imaging devices, and costs associated with internet and data management infrastructure. We will also model the improvement in clinical outcomes due to the earlier diagnosis of DR based on standard disease progression Markov models. Finally, we will integrate the findings from the disease progression and costing analyses to calculate the overall cost-effectiveness of our intervention in terms of additional costs incurred per incremental QALY gained or DALY averted.

